### Interpersonal therapy

Interpersonal therapy (IPT) is a manualised, time-limited psychological intervention for depression, implemented around the world. IPT focuses on four problems thought to trigger depression: grief, disputes, role transitions and social isolation. In IPT, individuals are encouraged to analyse and improve interpersonal relationships using techniques and strategies including linking mood to event and event to mood, role play and skill building. A meta-analysis of IPT for adolescents reported large reductions in depression (d = 1.48, *p* <.0001) [13]. IPT can be delivered by non-specialists in groups and is feasible in low-resource settings, but the evidence is inconsistent. In South Africa, group IPT for HIV positive adults reduced depressive symptoms compared to treatment as usual, but 21/41 participants allocated to IPT did not take it up [14]. In Uganda, group IPT for adolescents in internally displaced person camps improved depression among girls but not boys [15]. These findings highlight the need for research on IPT’s mechanisms and the contextual factors that influence them.

Between 2018 and 2022, we adapted the World Health Organization (WHO) group IPT manual for adolescents with depression in Nepal [16]. This involved translating the manual and reviewing it with Nepali mental health practitioners; conducting literature reviews on existing adaptations of IPT and concepts of mental health and interpersonal problems in Nepal; qualitative research with adolescents, caregivers, teachers and community health workers; consulting with a youth advisory board; and piloting the adapted manual with IPT trainers and facilitators [17, 18]. Key adaptations included integrating IPT into secondary schools, having separate groups for boys and girls, adding components to promote parental engagement and using locally acceptable terms for mental illness such as *man ko samasya* (heart-mind problem). We undertook an uncontrolled feasibility study of the intervention with 62 boys and girls aged 13–19 in Sindhupalchowk district, Nepal [19]. Adolescents attended 82.3% (standard deviation 18.9%) of group sessions. Depression improved between baseline and follow-up at 8–10 weeks post IPT: the Depression Self Rating Scale (DSRS) score decreased from 17.2 (95% confidence interval [CI]: 16.5–18,0) to 9.5 (95% CI 8.5–10.6) [19]. The estimated intervention unit cost was USD 96.9 with facilitators operating at capacity.

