Revision of exclusion criteria related to suicidal behaviour	In the pilot cRCT, we assessed suicidality using the Columbia Suicide Severity Rating Scale (CSSRS) and excluded adolescents with suicide intention or plan in the last two weeks or attempt within the last three months [30]. However, during the pilot cRCT, the team raised concerns about the specificity of the CSSRS, specifically that we were excluding adolescents who were not at high risk and could have benefitted from IPT. Consequently, we have undertaken extensive formative work to revise the CSSRS translation and our risk definitions, including interviews with adolescents and Nepali clinical experts. We will exclude high-risk adolescents defined as those with (i) suicide plan in the past 2 weeks, ii) suicide attempt in the past three months or iii) lifetime suicide attempt with suicidal ideation in the past two weeks.
Changes to data collection	
Timing the surveys relative to randomisation	We timed midline, endline and follow-up surveys in the pilot cRCT according to how far the intervention arm had progressed through the intervention (i.e. based on group session). This was difficult to operationalise because IPT groups progressed at different speeds due to school holidays, exams and absences, and it was not obvious when to conduct surveys with adolescents in the control arm. In the phase III trial, all surveys will be conducted based on time since randomisation (designated week 0).
Removal of second midline survey	We will not conduct a second midline survey in the phase III trial because we do not think the scientific insight from the survey justifies the resources required and burden imposed on adolescents and schools. Furthermore, the purpose of the midline survey is to identify the mechanism through which IPT improves depression (i.e., indirect effects). Data from the pilot trial revealed that the indirect effects were similar across the two midline surveys (week 3 and week 6).

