Surveys with mothers and fathers	In the pilot cRCT we assessed the feasibility of conducting surveys with a subgroup of adolescents’ mothers. We were able to collect data from 73% of mothers at baseline (40/55) including data on socioeconomic status and mental health. This suggests that it is feasible to conduct surveys with mothers in the phase III trial, but to improve the participation rate and reduce missing data we will conduct surveys with adolescents’ mother or father – whomever is available to participate. This will enable us to test hypotheses concerning the influence of parents’ socioeconomic status and mental health on adolescent trial outcomes.
Changes to implementation	
Strategies to optimise attendance at IPT sessions	We narrowly met progression criteria for attendance at IPT sessions in the pilot cRCT. To improve attendance in the phase III trial, we will introduce the following measures: • Optimising the timing of the intervention – we now have a detailed calendar of school holidays, closures and exam periods and therefore optimised the timing of the intervention to avoid these as much as possible. • Excluding grade 11 – in the pilot cRCT we combined grades 8/9 and 11 in some groups. Because of differences in class timetables for these grades we had few viable timeslots for IPT sessions. Timetables for grades 7, 8 and 9 have similar free periods and more mutually convenient timeslots, which will improve attendance. • Guidance on managing absenteeism in the IPT manual – this includes scripted conversation and motivational-interviewing techniques. • Showing a film to staff and students in intervention schools as part of an orientation session – we made a short film about IPT involving participants from the pilot trial to psychoeducate and destigmatise participation in IPT groups.

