### Study design

The trial is being implemented by Transcultural Psychosocial Organization Nepal (TPO Nepal) in partnership with University College London (UCL). We will conduct a superiority phase III cRCT to test whether IPT is more effective at reducing symptoms of adolescent depression compared to enhanced usual care. Schools are the unit of allocation and the trial will comprise 48 schools (24 intervention, 24 control).

Schools will be divided into eight groups or *waves* (six schools per wave). Advantages of grouping schools into eight waves include: (i) the duration between identifying that an adolescent is depressed at screening and the adolescent starting IPT is minimised; (ii) a staggered start to the surveys - meaning fewer research assistants and IPT facilitators are needed over the course of the trial; and (iii) randomisation can be conducted after the baseline survey with minimal delay. Schools will be allocated to each wave based on their location so that schools in the same area are allocated to the same wave. This will make it easier for the research and clinical teams to travel from school to school to provide supervision and oversight. Schools in each wave will be randomly allocated 1:1 to intervention/control conditions.

Within each wave, we will assess primary and secondary outcomes at baseline (pre-randomisation), endline (17 weeks’ post randomisation) and follow up (32 weeks’ post randomisation). We will also conduct a midline survey to assess intermediate outcomes five weeks after randomisation. The primary analysis will be a cross-sectional comparison of mean depression symptom scores at endline across trial arms, adjusted for baseline scores and clustering. Longer term follow-up will be conducted at 12-, 18- and 30-months post randomisation respectively.

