### Process evaluation data collection

The process evaluation design is informed by frameworks and theory including the general theory of implementation and Medical Research Council guidance [60, 61]. Process data will be quantitative and qualitative. We will collect core process evaluation data (including fidelity and acceptability) across all intervention schools and from all IPT participants. We will select 16 case study schools (eight in the intervention arm and eight in control) for in depth qualitative process data collection. We will purposively sample schools across different waves, municipalities and urban and rural areas. We will include smaller and larger schools. The process evaluation will assess intervention implementation, mechanisms of change and contextual factors.

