To assess acceptability, we will collect quantitative and qualitative data. In terms of quantitative data, across intervention schools, we will assess the percentage of IPT sessions attended by adolescents using information from facilitator attendance records (overall and by gender, caste/ethnicity and socioeconomic status). In all intervention schools, we will administer treatment satisfaction surveys to IPT participants in the last group session. In terms of qualitative data on acceptability, we will conduct interviews and focus group discussions with adolescents, caregivers and teachers in case study schools as well as facilitators and supervisors, using topic guides informed by the General Theory of Implementation [61]. We will explore: whether IPT is perceived as needed and valuable (coherence) and if this changes over the course of the intervention; how willing adolescents, families and schools were to invest in and commit to IPT (cognitive participation) and in what ways they demonstrated this commitment; how well IPT fitted into existing school and household routines (collective action); and how people felt IPT went (reflexive monitoring). We will also explore: intervention capability (whether IPT was workable within the education system); participant potential (individual and shared readiness for the intervention); institutional capacity (whether existing material and cognitive resources were sufficient, and how social norms and roles served to promote or undermine intervention activities); and contextual factors that affect intervention acceptability, for example whether implementation was better in schools that perceived a greater need and demonstrated more commitment to IPT.

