To describe enhanced usual care in the control arm, we will examine quantitative data on adolescent mental health service use in surveys, review case notes for participants referred to the counsellor (number of participants assessed, number of counselling sessions conducted, number and type of referrals made) and conduct focus group discussions with the counsellors. Contamination across arms is extremely unlikely and only possible if for example, a participant in a control school and participant from the intervention arm were in the same household or friendship group, or a participant from the intervention arm moves to a school in the control arm. Through surveys with parents, we will identify if any participants live in the same household. From IPT facilitator notes, we will be informed if any intervention participants move school.

Table 3 details qualitative and quantitative data sources for the process evaluation.

**Table 3 Tab3:** Qualitative and quantitative data sources for the process evaluation

Data source	Timing	No. of participants	No. of schools (intervention/control)	Evaluation domain addressed
Quantitative data				
Adolescent surveys	Baseline, midline, endline, follow up	480 to 768 (all participants)	*N* = 48 (Int: *N* = 24/Cont: *N* = 24)	Outcomes Contamination Mechanisms Context
Parent surveys	Baseline, endline	480 to 768 (parents of all participants)	*N* = 48 (Int: *N* = 24/Cont: *N* = 24)	Contamination Context
Facilitator competency assessments	Pre-training, post training, for each cycle and for each facilitator ENACT in pre-group sessions, GroupACT in 4 group sessions	All facilitators	N/A	Implementation
Session observations using IPT adherence checklist	Waves 1–8	All facilitators (~ 25% of total sessions)	*N* = 24 (I)	Implementation
School attendance records	Baseline, endline	480 to 768 (all participants)	*N* = 48 (Int: *N* = 24/Cont: *N* = 24)	Outcomes, implementation
IPT session attendance	Per each IPT session	240 to 384 (all intervention participants)	*N* = 24 (I)	Implementation
IPT treatment satisfaction survey	Endline	240 to 384 (all intervention participants)	*N* = 24 (I)	Implementation
Group cohesiveness assessment	Midline, endline	240 to 384 (all intervention participants)	*N* = 24 (I)	Implementation, mechanisms
Facilitator session and supervision records	Per each IPT session	All facilitators	N/A	Implementation, context

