To estimate indirect costs for the modified societal perspective, we will document productivity loss and informal care costs by recording adolescents’ time spent on intervention-related activities (including travel and participation) if relevant, as well as time and costs associated with outside healthcare utilisation. At endline and follow-up, we will collect data on adolescent health care visits since the baseline survey, including the time and out-of-pocket expense for each visit (across a range of non-school based formal and informal healthcare types available locally). For each type of healthcare service received, we will establish whether its cost is fully covered by out-of-pocket expenditures, or whether it was partially or fully subsidised by the provider. We will record the estimated subsidised cost of services using publicly available information; if subsidised costs are not available, we will contact service providers to establish appropriate estimates or ranges which will be tested in sensitivity analyses. We will collect productivity and informal care costs from interviews with all available parents at endline and follow-up, documenting the time parents have spent providing care as well as opportunity costs of care-seeking for both parents and adolescents. Adolescents will be asked about any earnings from paid work and opportunity costs of healthcare utilisation at midline, endline, and all follow-up surveys. Intervention participants will also be asked about opportunity costs of IPT attendance at midline and endline during group cohesion assessments to maintain masking of group allocation. Cost data will be collected prospectively throughout the trial in Nepali rupees (NPR) and reported in 2024 prices.

The primary health outcome of interest for the economic evaluation analyses is the quality-adjusted life year (QALY). QALYs will be calculated using EQ-5D-5 L health utility scores from adolescents at each planned timepoint for data collection. Using this data, we will derive QALY weights using existing value sets from India, which represent the closest cultural context for which EQ-5D-5 L value sets are available [65].

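### The text places the treatment satisfaction survey in the last group session, but Table 3 places it at endline for all intervention participants; a last-session survey would miss absentees and may overstate satisfaction

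*Protocol article*

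**What the plan says.** Three places in the protocol article describe how satisfaction or acceptability data are collected.

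- Implementation section, on acceptability: "In all intervention schools, we will administer treatment satisfaction surveys to IPT participants in the last group session". No route is given for adolescents who are not there.
- Table 3, row for the IPT treatment satisfaction survey: timing is endline, the setting is all 24 intervention schools, and the number is "240 to 384 (all intervention participants").
- Process evaluation data collection, opening paragraph: "We will collect core process evaluation data (including fidelity and acceptability) across all intervention schools and from all IPT participants".

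Endline is defined by the calendar and not by session number. The Study design section gives "endline (17 weeks’ post randomisation"), and Table 1 explains: "In the phase III trial, all surveys will be conducted based on time since randomisation (designated week 0"). Table 1 gives as the reason that groups moved through the sessions at different speeds in the pilot.

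On attendance, the Interpersonal therapy section reports from the feasibility study: "Adolescents attended 82.3% (standard deviation 18.9%) of group sessions". For the pilot, Table 1 says: "We narrowly met progression criteria for attendance at IPT sessions in the pilot cRCT", without a figure.

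**The concern.** Acceptability is part of objective iv, and the satisfaction survey is the only structured measure of satisfaction described for the whole intervention arm. Collected in the last session, it depends on attendance, which the protocol itself treats as an acceptability measure.

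The protocol also gives reasons to expect absentees to differ from attenders. In Table 4, H7 predicts lower attendance among the poorest adolescents, and H15 predicts lower attendance and worsening depression among those who meet stigma. The section on the theory of change reports that pilot participants in extreme adversity often could not attend. If these adolescents are also less satisfied, a last-session score describes those who stayed, while Table 3 labels it as describing everyone allocated.

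**Working it through.** **Reproducing Table 3.** The Power and sample size section plans 24 schools per arm and 10 to 16 adolescents per school: 24 × 10 = 240 and 24 × 16 = 384. The number in Table 3 is therefore the whole planned intervention arm, with no allowance for absence.

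**Do the two timings coincide?** The Intervention section has two pre-group and ten group sessions, generally weekly, so about 12 weeks if nothing slips. Endline is at week 17. Sessions that start promptly and run to schedule would finish about 5 weeks before endline. A delayed group could finish close to endline or after it. The last session and endline are thus different time points, with a gap that varies by group.

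**How many would a last-session survey miss?** Missed = N × (1 − share present). The share present at session 10 is not given, so it is assumed here. The middle value is the feasibility mean over all group sessions; the other two bracket it.

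| Assumed share present | Reached, of 240 / 384 | Missed, of 240 / 384 |
|---|---|---|
| 95% | 228 / 365 | 12 / 19 |
| 82.3% | 198 / 316 | 42 / 68 |
| 70% | 168 / 269 | 72 / 115 |

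**How far could the satisfied share be overstated?** Overstatement = (1 − share present) × (satisfied share among those present − satisfied share among those absent). The difference in satisfaction is also not given and is assumed.

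| Assumed share present | Absentees equal | 10 points lower | 20 points lower | 40 points lower |
|---|---|---|---|---|
| 95% | 0 | 0.5 | 1.0 | 2.0 |
| 82.3% | 0 | 1.8 | 3.5 | 7.1 |
| 70% | 0 | 3.0 | 6.0 | 12.0 |

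Entries are percentage points. For example, at 82.3% present and a 40-point difference: 0.177 × 40 = 7.1.

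**The case against.** The text does not say that absentees are skipped, and both Table 3 and the process evaluation introduction say that all participants are covered. A condensed article may leave catch-up arrangements to the full protocol, and endline in Table 3 may be a loose label for the end of treatment. This is fair: the documents do not establish that only attenders will be surveyed. What stands is that the article fixes a collection point that does not fit its own table, in timing or in coverage.

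Satisfaction is also only one part of acceptability. Attendance is recorded for every intervention participant and broken down by gender, caste or ethnicity and socioeconomic status. H7 is tested on those records. H15 uses stigma questions in the endline adolescent survey, which does not depend on attending session 10. Interviews and focus groups add to this. That objection stands in full and confines the point to the satisfaction score. It does not remove the point, because attendance records show who was absent and not what they thought of IPT, and the qualitative work covers 32 IPT adolescents in case study schools.

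The size is unknown. The 82.3% comes from 62 adolescents in another district and averages over all sessions, one-off absences included. Table 1 lists measures to raise attendance in this trial. If absentees are as satisfied as attenders, there is no bias.

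Finally, the endline cohesion assessment proposed below carries the same all-participants label in Table 3, and nothing shows how it reaches adolescents who have left their group. That also stands, and the fix has to deal with it.

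**Conclusion.** The inconsistency is firm: last session in the text; endline and the full 240 to 384 in Table 3; all IPT participants in the process evaluation introduction. If the text is followed as written, selection towards a favourable satisfaction score is a real risk. At an assumed 82.3% present, 42 of 240 to 68 of 384 adolescents would have no data, and the satisfied share would be overstated by 0 to about 7 percentage points for assumed differences of 0 to 40 points. At an assumed 70% present the upper end is 12 points.

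A reader might infer three stronger conclusions that the documents do not support:

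- *The acceptability assessment as a whole leaves out those who stopped and will be too favourable.* Attendance data count non-attendance directly, and the direction and size of any bias in the satisfaction score rest on assumptions.
- *At least 18% will be missed.* The feasibility mean is not last-session attendance and sets no floor.
- *A biased satisfaction score would drive the scale-up decision.* The abstract ties scale-up to effectiveness and the Discussion ties it to cost-effectiveness; no satisfaction threshold appears.

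Severity is low. The measure is a descriptive process measure, and the primary outcome is unaffected.

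**What to change.** Reconcile the Implementation text with Table 3 and the process evaluation introduction:

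1. Offer the satisfaction questionnaire to every adolescent allocated to IPT, whatever their attendance, at the endline group cohesion assessment in the intervention arm. The Economic evaluation data collection section already places IPT-specific questions there, "during group cohesion assessments to maintain masking of group allocation". If the last-session form is kept, use that contact at least for those absent from the last session.
2. State how adolescents who have left their group are reached at that contact, and keep the questionnaire apart from the outcome survey run by masked research assistants, because its content reveals allocation.
3. Report the number responding out of all allocated, and satisfaction by sessions attended.

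The cost is a wording change and one short questionnaire at a contact already planned, plus some effort to trace those who have left. Recall is somewhat longer where endline falls after the last session. IPT began in Waves 1 and 2 in June and July 2025, so any data already collected in the last session should be reported as such; recruitment runs to November 2026, so later waves can still benefit.

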### Mechanisms of change and contextual factors

Informed by realist evaluation principles and work by Bonell and colleagues on realist randomised trial methodology [20, 21, 62], the process evaluation seeks to refine our theory of change about how IPT works, for whom and in what circumstances. To do this, we have generated hypotheses in the form of CMOCs about how intervention mechanisms and contextual factors interact to generate outcomes. We define mechanisms as changes in the reasoning and behaviour of individuals or the way in which institutions operate in response to local use of intervention resources [21]. Whilst mechanisms cannot be directly observed they can be inferred for example through quantitative data on mediator variables or qualitative data collected from intervention participants. We define context as aspects of the place or people within which an intervention is implemented that might affect how the mechanisms operate. Context can relate to material or non-material features (social, psychological, organisational, political and economic), and operate at all levels of the social ecological framework including individual, family, school, community and government levels.

We also propose ‘dark logic’ hypotheses related to mechanisms of potential harm, where mechanisms of harm might generate ‘paradoxical effects’ on our primary or secondary outcomes or generate ‘harmful externalities’ in other domains [63].

We will draw on findings from analyses of the qualitative process data to refine (including removing or adding to) our hypotheses. This ensures we remain open to pathways that are not already specified in our process evaluation. We will then test these refined hypotheses using analyses drawing on quantitative trial data to check these data align with our theoretical predictions [62]. We will use mediation analyses to examine underlying mechanisms that explain the effect of IPT on adolescent depression. Moderation analysis will be used to assess whether a measure of contextual factor moderates the effect of IPT on depression. We will also use moderated mediation analysis to test whether mediation is contingent on a contextual factor.

We use categories proposed by Bonell and colleagues in a previous realist RCT to organise our hypotheses [64]. These categories are intervention mediators, contextual factors affecting implementation, contextual factors modifying intervention effects and potential harms. Table 4 presents our CMOCs and indicates the data and analyses we will use to test them.

**Table 4 Tab4:** Process evaluation hypotheses and associated data and analyses

Hypotheses	Qualitative data sources/analyses	Quantitative data sources/analyses
Hypotheses about intervention mediators		
H1: Adolescents participating in IPT will report increased social support at midline, endline and follow up due to bonding between group members, initiation of new relationships outside groups and/or improvement in the quality of existing relationships. This generates reductions in depression.	Analysis of SSI transcripts with adolescents and parents and FGD transcripts with facilitators from different groups (direct and indirect probing on hypothesis)	Mediation analysis to assess if IPT affects PHQ-A outcomes at endline through social support (MSPSS score at midline)
H2: Adolescents participating in IPT will report reduced interpersonal conflict at midline, endline and follow-up due to improved communication of interpersonal needs and strategies to better manage anger. This generates reductions in depression.	Analysis of SSI and FGD transcripts with adolescents and facilitators from different groups (direct and indirect probing on hypothesis)	Mediation analysis to assess if IPT affects PHQ-A outcomes at endline through interpersonal conflict (Social Adjustment Scale Self Report score at midline)
H3: Adolescents participating in IPT will experience improved emotion regulation at midline, endline and follow up because they learn how to name and express their emotions. This generates reductions in depression.	Analysis of SSI transcripts with adolescents and parents and FGD transcripts with facilitators from different groups (direct and indirect probing on hypothesis)	Mediation analysis of adolescent survey data (DERS-SF and PHQ-A outcomes)
H4: Adolescents participating in IPT will report increased hope at midline as participants perceive the possibility of change in mood and relationships. This generates reductions in depression.	Analysis of SSI transcripts with adolescents	Mediation analysis of adolescent survey data (Herth Hope Index and PHQ-A data)
H5: Adolescents participating in IPT will report improved self-efficacy at midline, endline and follow-up because they experience generating solutions to and solving their interpersonal problems. This generates reductions in depression.	Analysis of SSI transcripts with adolescents and FGD transcripts with facilitators from different groups	Mediation analysis of adolescent survey data to assess if self-efficacy mediates PHQ-A.
H6: Adolescents participating in IPT will report improved self-compassion at midline, endline and follow up because in IPT groups they normalise and validate their experience of depression. This generates reductions in depression.	Analysis of SSI transcripts with adolescents and FGD transcripts with facilitators from different groups	We will not have quantitative data to test this hypothesis.
Hypotheses about contextual factors affecting implementation		
H7: Adolescents participating in IPT who are from the poorest backgrounds whose basic needs are not met will attend fewer IPT sessions because they have to undertake paid work and/or have household responsibilities to fulfil.	Analysis of SSI transcripts with adolescent and parents and FGD transcripts with facilitators from different groups (direct and indirect probing on hypothesis)	Analysis of adolescent IPT session attendance data and socio-demographic data from baseline survey
H8: Groups involving adolescents across two grades (8/9) rather than three (7/8/9) will be more cohesive and attendance among participants will be higher because participants will be closer in age and maturity and sessions will be easier to schedule across fewer timetables.	Analysis of FGD transcripts with facilitators and SSIs transcripts with teachers (direct and indirect probing on hypothesis)	Analysis of group cohesion and adolescent IPT session attendance data.
H9: In schools that have experienced a suicide, an attempted suicide or mass conversion disorder (chopnne), IPT will be more acceptable and implemented with more fidelity because staff will be more motivated to support the programme.	Analysis of SSI transcripts with teachers and principals, FGD transcripts with facilitators	We will not have quantitative data to test this hypothesis.
Hypotheses about contextual factors influencing intervention effects (CMOCs)		
H10: Adolescents participating in IPT who attend schools with a climate characterised by a lack of understanding and supportive teacher and student relationships (context), will build strong peer to peer social support, a group identity and a sense of belonging with IPT group members (mechanism) that will offset the negative effect of the school climate on adolescents’ depression (outcome).	Analysis of SSI transcripts with adolescents sampled to represent different school climates (baseline Beyond Blue score), teachers and principals, and FGDs with facilitators, probing on hypothesis	Comparison of group cohesion data across schools Moderator analysis of adolescent survey data (Beyond Blues School Climate Scale as moderator variable, PHQ-A outcome)
H11: Adolescents participating in IPT from a lower socioeconomic background (poorer household, context) will be more engaged and motivated to address their problems and have more problems to solve compared to their peers from wealthier backgrounds. These adolescents will share their feelings and problems and participate in discussions through which they learn strategies to regulate their emotions, reduce conflict, build social support and improve self-efficacy (mechanism) and therefore experience more benefit from IPT compared to peers from a higher socioeconomic background (outcome).	Analysis of SSI transcripts with adolescents from different socioeconomic backgrounds and facilitator FGD transcripts (direct and indirect probing on hypothesis)	Moderator analysis of adolescent survey data (socioeconomic moderator variable and PHQ-A outcome)
H12: For girls, who are subject to gender norms that discourage them from expressing their feelings (context), group IPT will serve as a platform to become aware of and share feelings and learn emotion regulation skills (mechanism) which reduce their depression. On the other hand, boys who are exposed to gender norms which promote aggression and anger (context), through IPT learn how to reduce interpersonal conflict (mechanism) and therefore experience reductions in depression (outcome).	Analysis of SSI transcripts with boys and girls, and facilitator FGD transcripts (direct and indirect probing on hypothesis)	Moderated mediation analysis of adolescent survey data (gender moderator, emotion regulation and conflict mediator variables, PHQ-A outcome)
H13: For adolescents with a parent who has a mental health problem (context), through IPT they will increase their social support, normalise and validate their feelings, generate and implement solutions to their problems and reduce conflict at home (mechanism). This will offset the effect of the parent’s mental health on the adolescent’s depression (outcome).	Analysis of SSI transcripts with adolescent and parents with and without mental health problems (GHQ-12 score at baseline) and FGD transcripts with facilitators from different groups (direct and indirect probing on hypothesis)	Moderator analysis to assess if parent GHQ-12 score at baseline moderates effect of IPT on PHQ-A score at endline
Hypotheses about potential harms		
H14: For adolescents with a background of trauma (context), who recount their traumatic experiences during group sessions and to whose experiences other group members cannot relate, IPT will exacerbate their distress due to re-experiencing the stressful event (mechanism), which will result in a worsening of depression (outcome).	Analysis of SSI transcripts with adolescents with and without trauma (baseline PCL score) and FGD transcripts with facilitators from different groups (direct and indirect probing on hypothesis)	Analysis of adolescent survey data (PCL, PHQ-A outcomes)
H15: Adolescents experiencing stigma from school and community members because of their participation in IPT (context) would attend fewer sessions and the stigma would cause them distress and their depression worsens.	Analysis of SSI transcripts with adolescents who have experienced stigma and facilitator FGD transcripts	Cross-sectional analysis of adolescent survey data (endline, questions about experience of stigma due to participation in IPT, PHQ-A
H16: In groups adolescents are encouraged to generate and select solutions to solve their interpersonal problems. If the group is poorly facilitated these solutions may run counter to our theory of change and could cause adolescents harm for example by inciting violence in the context of a dispute. This could exacerbate adolescents’ depressive symptoms.	Analysis of SSI transcripts with adolescents and facilitator FGD transcripts probing on the nature of solutions generated within groups and their consequences Analysis of information from facilitator session and supervision notes on solutions and consequences	We will not have quantitative data to test this hypothesis.
H17: Group members or facilitators may breach an adolescent’s confidentiality by disclosing sensitive information about them to individuals outside the group. This would be distressing for the adolescent and could have harmful consequences resulting in the worsening of their depression.	Analysis of SSI transcripts with adolescents and facilitator FGD transcripts probing for evidence of a breach in confidentiality	We will not have quantitative data to test this hypothesis.

